### 11.2 Statistical analysis

#### 11.2.1 Baseline characteristics

Differences in baseline characteristics between intervention and control groups will be tested using independent t-tests, Mann Whitney U tests and chi-square tests.

#### 11.2.2 Primary analysis

Data will be analyzed on an intention-to-treat basis: patients who have been randomized to the intervention group but for whatever reason do not start or continue with training, will be encouraged to still undergo the assessments. Additionally, a per-protocol analysis will be performed with the patients who have completed at least 75% of the training sessions. Longitudinal regression analysis will be used to assess changes in each outcome measure. The two follow-up measurements will be defined as dependent variable and multi-level analysis with three levels will be used, 1) treatment center 2) time of follow-up measurement (values corresponding with performance at  $t=1$  and  $t=2$ ); 3) individual.

Regression coefficients indicate differences between intervention and control group. Regression models will be adjusted for baseline values, age and gender. To test our hypothesis that the changes in physical fitness will mediate, in part, the beneficial effect of exercise on fatigue and quality of life, a mediation analysis will be performed using Latent variable structural equation modelling.

For *hypothesis 3* scores on the self-reported measures of mood state, physical activity and HRQL will be calculated according to existing scoring algorithms. Next multilevel longitudinal regression analyses will be conducted to assess differences in each outcome measure between intervention and control group at follow-up. Regression coefficients indicate differences between intervention and control groups.

Regression models will be adjusted for gender, age and baseline values. For *hypothesis 4* (examining the differences in return to work), we will use Kaplan Meier's and the Cox proportional hazard regression for recurrent events. The general idea behind this analysis is that the different time periods are analysed separately adjusted for the fact that the time periods within one patient are dependent. Recurrences of sick leave for any reason during follow-up will be added to the Cox proportional hazards model with the

time to event approach, in which only the transitions from sick leave to return to work are taken into account.

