### 7.2 Randomized controlled trial

This multicenter, prospective, single blind, RCT will compare an exercise intervention and standard care with standard care only. The 120 patients participating in the study will be randomized to either the intervention arm (n = 60) or the control arm (n = 60). In addition to the standard care, patients in the intervention arm will take part in an 18-week individualized supervised high-intensity exercise program. This program will start 6-14 weeks after SCT. Patients in the control group are treated according to standard care.

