#### 8.1.3 Counseling

A behavioural motivation component is included to improve compliance and to stimulate physical activity outside the exercise program in addition to and after completion of the exercise program. From week 12 onwards patients are encouraged to meet the recommendations made by the American College of Sports Medicine and the American Heart Association [33]. Specific program elements include the provision of general and motivational information, both verbally and via folders, about physical activity and the desired intensity of activity based on the Borg Scale rating perceived exertion [34]. The physiotherapist uses basic counselling techniques and instruction sheets.

Table 1. Structure of the exercise program

| Week                                                                                                           | Type of training                                           | Number of training sessions | Aim of the training                                                                                                                                                                                                                                                       |
|----------------------------------------------------------------------------------------------------------------|------------------------------------------------------------|-----------------------------|---------------------------------------------------------------------------------------------------------------------------------------------------------------------------------------------------------------------------------------------------------------------------|
| 1-12                                                                                                           | Resistance training and interval training (2 x 8 minutes). | 2x per week, 60 minutes.    | 1. improve coordination and muscle hypertrophy and hereby improving muscle force.
2. become familiar with exercise program.
3. increasing aerobic capacity.
4. overcoming the fear of physical activity.
5. increasing the pleasure in being physical active. |

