| 13-18                                                                                                          | Resistance training and interval training (2 x 8 minutes). | 1 x per week, 60 minutes.   | 1. promote independence.
2. maintain muscle force.
3. improve muscle endurance.
4. improve aerobic capacity.                                                                                                                                                     |
| 1, 4, 10, 12, 18, 22                                                                                           | Counseling.                                                | 6 x 15 minutes              | 1. encourage patients to pursue an active lifestyle.
2. give information about desired intensity and duration of physical activities.
3. fill out the activity diary.                                                                                               |
| Training: 30 sessions a 60 minutes = 30 hours
Counseling: 6 sessions a 15 minutes = 1.5 hours |                                                            |                             |                                                                                                                                                                                                                                                                           |

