## 11. Statistical considerations

### 11.1 Sample size and statistical power calculations

The sample size calculations were estimated for the primary outcomes for a two-sided  $\alpha=0.05$ , and a power of 80%. We expect a between group difference of  $7.5\pm 7$  ml/kg/min in VO2 max, of  $0.2\pm 0.1$  kg in hand grip strength and of  $3.5\pm 4$  in fatigue (MFI). We need between 25 and 42 subjects per group to detect these differences between the intervention and control group. Assuming a dropout rate of 30% (15% of the patients in our database who had undergone autologous SCT for MM< HL or NHL have an early relapse within 6 months, and are therefore expected not to complete the intervention program, and may in addition not be able to complete the study assessments. Furthermore, 15% may drop out because of other reasons) we need to enrol 60 subjects per group.

In the five participating transplant centers, yearly 180-210 autologous SCT are being performed. In 2007 170 patients received an autologous SCT for MM, HL or NHL (MM: 105 patients; NHL: 55 patients, HL: 10 patients). Taking in consideration all patients who will be ineligible for randomization (treatment related mortality SCT 4.3% = 3 patients; 10% of MM patients receiving an allogeneic SCT = 11 patients; 20% of MM patients having extensive osteolytic lesions with risk of fracture = 22 patients) we estimate that of the 170 patients transplanted yearly, 137 will be eligible, the majority of whom are expected to be interested in participating in the study (60 patients are needed on a yearly basis). This indicates that the proposed study is feasible with a projected inclusion time of 2 years.

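### The additional per-protocol set is defined by a criterion only the exercise arm can fail: it leaves no controls if read literally, and a contrast expected to favour exercise if all controls are kept.

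*Protocol*

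**What the plan says.** Protocol section 11.2.2 sets the main approach: "Data will be analyzed on an intention-to-treat basis". It then adds that "a per-protocol analysis will be performed with the patients who have completed at least 75% of the training sessions". No other criterion for this set is given, and nothing says which controls belong to it. The regression models adjust for baseline value, age and gender.

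Table 1 gives the exercise arm its denominator: "Training: 30 sessions a 60 minutes = 30 hours". The control arm has none, since section 7.2 says "Patients in the control group are treated according to standard care".

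Section 11.1 plans for 30% dropout, half from early relapse and half from other reasons. Of the relapsing 15% it says that they "have an early relapse within 6 months, and are therefore expected not to complete the intervention program", and that they may also miss study assessments. Section 8.3 lists early relapse, injury or disease, non-compliance and death among the reasons for leaving protocol treatment. Section 9.4 says that subjects who withdraw from treatment will still be asked to take part in follow-up measurements.

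**The concern.** Attendance is observed after randomisation and exists in one arm only. The protocol itself expects patients who relapse early to fall short on it. The rule therefore tends to take patients with a poor course out of the exercise arm. Nothing takes their counterparts out of the control arm, except missing assessments. Adjusting for baseline value, age and gender cannot correct for relapse that occurs after randomisation.

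With no true effect of exercise, the per-protocol contrast could then still be expected to show a benefit. The analysis is prespecified under the heading of the primary analysis and would stand beside the intention-to-treat result, where it could be taken as the effect of exercise in patients who actually train. On the literal reading the problem is more basic: a set made up only of patients who completed sessions allows no comparison between arms.

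**Working it through.** **The protocol's own figures.** Evaluable patients per group at the upper end: 42 (section 11.1). Dropout: 30%. Enrolment: 42 / (1 − 0.30) = 60 per group, as stated. Sessions: 12 × 2 + 6 × 1 = 30, as in Table 1; 75% of 30 is 22.5, so a patient needs at least 23.

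**Who the rule removes.** On the section 11.1 rates, up to 18 of 60 exercise patients fail it: 0.15 × 60 = 9 with early relapse and 9 for other reasons. About 42 remain. About 18 controls are of the same type, and the rule removes none of them.

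**Assumptions, because the protocol gives no figure.** D is the deficit, in SD, of the removed type of patient. f is the share of such controls who are assessed. There is no true exercise effect.

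**Bias from relapse alone.** Bias ≈ 0.15 × f × D.

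- f = 0: bias 0 for any D.
- f = 0.5, D = 0.5: 0.0375 SD.
- f = 1, D = 0.5: 0.075 SD.
- f = 1, D = 1.0: 0.15 SD.
- f = 1, D = 1.5: 0.225 SD.

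On the protocol's VO2max SD of 7 ml/kg/min, 0.0375 to 0.225 SD is 0.26 to 1.58 ml/kg/min. The expected difference is 7.5.

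**Type I error.** Take 42 exercise patients against 51 controls (42 + 9 relapsed). SE = sqrt(1/42 + 1/51) = 0.208 SD. Error = Φ(bias/SE − 1.96) + Φ(−bias/SE − 1.96).

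| Bias (SD) | Two-sided type I error |
|---|---|
| 0 | 5.0% |
| 0.0375 | 5.4% |
| 0.075 | 6.5% |
| 0.15 | 11.1% |
| 0.225 | 19.1% |

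The multiplier 0.15 is slightly low for 51 controls, where the relapsed share is 9/51 = 17.6%. With that share the full-assessment biases become 0.09, 0.18 and 0.26 SD. The picture does not change.

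**Bias from all expected non-completers.** If all 18 such controls are assessed, bias = 0.30 × D, with 42 against 60 patients (SE 0.201 SD).

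- D = 0.25: 0.075 SD, type I error 6.6%.
- D = 0.5: 0.15 SD (1.05 ml/kg/min, or 0.6 MFI points on the stated SD of 4), 11.6%.
- D = 1.0: 0.30 SD, 32%.

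A simulation of 20,000 trials, with 30% non-completers drawn at random in each arm, gave 6.6%, 11.2% and 28.1%. Intention-to-treat with everyone assessed stayed at 5%. If only half of these controls are assessed, their share is 9/51 = 17.6% and the biases fall to 0.04, 0.09 and 0.18 SD. If none are assessed, the bias is 0.

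**The case against.** **The analysis is only additional.** This stands. Intention-to-treat is the stated basis, the economic evaluation follows it too, and no sample size rests on the per-protocol set. A reader might infer that the trial's main conclusion is biased; the protocol does not support that.

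**The text has no rule for controls, and the analysis plan may supply one.** Half of this stands. Keeping all controls is an inference, and the literal reading gives no controls. But the point is not an omission: the criterion that the protocol does fix is one that only one arm can fail.

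**Relapsed controls may not be assessed.** This stands as a limit on size. Section 11.1 counts relapse inside the 30% that reduces 60 to 42 in each group; if those patients are missing from both arms, the bias from relapse is zero. Yet the section says only that they may miss assessments, and section 9.4 seeks follow-up after withdrawal. A reader might infer that a spurious benefit is certain, or that type I error will be 11% to 19%. Those rates need deficits of 1.0 to 1.5 SD, which the document does not give, and every relapsed control assessed. At 0.5 SD with full assessment the rate is 6.5%.

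**Not every relapse is removed.** True: a patient who relapses after the 23rd session stays in. A reader might also fault the threshold because weeks 1–12 hold 24 of 30 sessions (80%). Skipping all of weeks 13–18 would take 23 of the first 24 sessions, which is high attendance, so this is no defect in itself.

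**The usual remedy has its own bias.** This stands. Randomisation as instrument for reaching 75% assumes no benefit below 75%. Suppose 70% of patients comply with effect 1.0 and 30% attend less with effect 0.5. The intention-to-treat effect is 0.70 × 1.0 + 0.30 × 0.5 = 0.85, and the instrumental-variable estimate is 0.85 / 0.70 = 1.21, which is 21% too high. The assumption must be stated.

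**Conclusion.** The point holds for the additional per-protocol analysis only. As written, its set either contains no controls or, if all controls are kept, gives a contrast expected to favour exercise. That direction rests on two conditions: relapsed or otherwise non-adherent types of control are assessed, and they score worse. Both are plausible, but neither is quantified in the protocol.

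Under 15% relapse and an assumed deficit of 0.5 to 1.5 SD, the bias from relapse lies between 0 and about 0.22 SD, with type I error between 5% and about 19%. With all 30% expected non-completers counted, the upper limit is 0.30 times the deficit. These are illustrations of range, not predictions. The definition should be corrected before the data are analysed.

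**What to change.** Replace the per-protocol contrast in section 11.2.2 by an instrumental-variable estimate in all randomised patients, with randomisation as instrument and the covariates of the primary model. Preferably use the number or proportion of sessions attended as the exposure, and state the assumption that the effect is linear in attendance. If the 75% cut-off is kept as the exposure, state the assumption of no effect below it.

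If a per-protocol table is still wanted:

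- state which controls enter it;
- exclude relapse before T1 in both arms;
- note that other non-adherence is still removed from the exercise arm only;
- label the table supportive and descriptive.

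The cost is a change of wording and a few hours of programming. Attendance (section 9.4) and relapse (section 9.3) are already recorded, so no new data are needed. The price is a wider confidence interval than that of the naive contrast, and reliance on the stated attendance assumption.

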## 6. Study Objectives

Primary objective:

- To evaluate the effectiveness of a state-of-the-art individualized high-intensity exercise program in comparison to standard care with respect to fatigue, physical fitness, and HRQoL in patients with hematologic malignancies who have undergone HDT and autologous SCT.

Secondary objective:

- To evaluate the cost-effectiveness of this exercise program in comparison to standard care.

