## 9. Outcome measures

### 9.1 Primary outcome measures:

#### 1. Cardiopulmonary fitness

Cardiopulmonary fitness is related to the ability to perform large muscle, dynamic, moderate-to-high intensity exercise for prolonged periods. Performance of such exercise depends on the functional state of the respiratory, cardiovascular, and skeletal muscle systems.  $\text{VO}_{2\text{ max}}$  testing is well established and there are international guidelines concerning standardization and interpretation strategies [37]. This technique has been shown feasible in cancer survivors [4]. The  $\text{VO}_{2\text{ max}}$  test will be performed on a cycle ergometer and a ramp test design will be used. ECG, saturation and blood pressure will be monitored and heart rate (HR) and gas exchange variables will be recorded continuously. The test will be supervised by a physician.

By applying this test a broad range of parameters can be assessed. Among these parameters are the

- Maximal work rate (Wmax)
- Ventilation threshold (VT)
- $\text{VO}_2$  at VT ( $\text{VO}_2\text{ VT}$ )
- Maximal ventilation ( $\text{V}_E\text{ max}$ )
- Maximal respiratory frequency (f max)
- $\text{VO}_2$  at respiratory exchange ratio = 1 ( $\text{VO}_2\text{ RER } 1$ )
- HR at respiratory exchange ratio = 1 ( $\text{HR RER } 1$ )
- Maximal aerobic power ( $\text{VO}_{2\text{ max}}$ )
- Maximal HR (HRmax)
- HR at VT (HR VT)
- % Saturation of Hb with  $\text{O}_2$  (S)

Prior to the aerobic exercise test pulmonary function will be assessed at rest by measuring the forced air expiratory volume in 1 second (FEV-1), the forced vital capacity (VC), inspiratory capacity (IC) and the maximal voluntary ventilation (MVV) using a portable spirometer [38].

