#### 2. Muscular strength

Muscular strength refers to the external force that can be generated by a specific muscle or muscle group. Upper extremity muscular strength will be assessed using a grip strength dynamometer and lower extremity muscular strength by the '30 s chair stands' test. In addition muscular strength of the m. quadriceps will be measured isometrically using a fixed dynamometer (Biodex System).

Maximal handgrip strength is performed three times for each hand. The mean score attained for each side will be recorded. The '30 s chair stand' test has been demonstrated to be a valid and reliable measure of proximal lower limb strength in older adults. The subject is asked to stand upright from a chair with arms folded across the chest, then to sit down again and then repeat the action at his/her own/fastest pace over a 30 s period. The final test score is the number of times that the subject rises to a full stand from the seated position with arms folded within 30 s [39]. To assess the strength of the m. quadriceps, patients will also be asked to perform three maximal voluntary knee extensions with the dominant leg at 60 degrees knee angle. The highest peak torque (Nm) of the three attempts will be used for analysis.

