#### 3. Fatigue

Two self-report questionnaires will be used to assess fatigue: the Multidimensional Fatigue Inventory (MFI) and the Fatigue Quality List (FQL). The MFI is a questionnaire consisting of 20 statements for which the person has to indicate on a 0-5 scale to what extent the particular statement applies to him or her. The statement refers to aspects of fatigue experienced during the previous days. Higher scores indicate a higher degree of fatigue. This self-report instrument consists of five subscales based on different dimensions: general fatigue, physical fatigue, reduced activity, reduced motivation and mental fatigue [40,41].

The patients' perception and appraisal of experienced fatigue will be assessed with the FQL [42]. The FQL consists of 25 adjectives describing the fatigue experience, organized into 4 subscales: frustrating, exhausting, pleasant, and frightening. An exploratory hypothesis is that, even if levels of fatigue severity do not change significantly over time, the subjective experience and perceived meaning of the fatigue may change as a function of physical exercise (e.g., from frustrating to pleasant, due to attributing the symptoms of fatigue to physical exertion rather than effects of the disease or its treatment). This necessitates the use of 2 questionnaires for measuring fatigue.

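### The primary outcome is not fixed: section 9.1 makes three whole domains primary, 11.1 sizes on one measure each, and no contrast, success rule or error control joins them, so false-positive risk is about 14% or more if any one result counts

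*Protocol*

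**What the plan says.** **Objective (Protocol section 6; the Summary in section 4 agrees).** The primary objective covers effectiveness "with respect to fatigue, physical fitness, and HRQoL in patients with hematologic malignancies".

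**Primary outcomes (section 9.1).** Three domains are listed.
- *Cardiopulmonary fitness:* "By applying this test a broad range of parameters can be assessed". Eleven exercise-test values follow, VO2max among them, and then four resting lung-function values under the same heading.
- *Muscular strength:* hand grip, where "The mean score attained for each side will be recorded", the 30-second chair stand, and isometric quadriceps torque.
- *Fatigue:* the MFI with five subscales and the Fatigue Quality List (FQL) with four. The reason given for the FQL begins "An exploratory hypothesis is that, even if levels of fatigue severity do not change significantly over time".

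No domain has a lead variable. Section 9.2 places health-related quality of life among the secondary outcomes.

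**Sample size (section 11.1).** "The sample size calculations were estimated for the primary outcomes for a two-sided" alpha of 0.05 and 80% power. One measure per domain is used: VO2max, hand grip strength and MFI fatigue.

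**Analysis (section 11.2.2).** "Longitudinal regression analysis will be used to assess changes in each outcome measure". The values at t=1 and t=2 together form the dependent variable of one multilevel model, adjusted for baseline, age and gender.

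**The concern.** These sections give different answers to the question of what is primary. Section 6 includes quality of life and section 9.2 demotes it. Section 9.1 offers whole domains. Section 11.1 implies one measure in each, but leaves open which MFI score is meant and how left and right grip are combined. Section 11.2.2 applies the same regression to everything. It does not say whether the treatment effect of interest is at t=1, at t=2 or averaged over both, nor whether one, two or all three domains must be positive.

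The FQL adds a difficulty. It sits in a primary domain, yet the reason for it is to detect a change in how fatigue is experienced when fatigue severity does not change. It is therefore a second route to a positive fatigue result.

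At stake is the main conclusion. A reader could not tell whether a favourable result was the one the trial was built to test or one of several that could have been put forward. The ambiguity also reaches the cost-effectiveness ratios in section 11.2.3, which are built on the primary clinical effect measures.

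**Working it through.** **1. The plan's own figures.** Section 11.1 gives mean difference ± SD of 7.5 ± 7 (VO2max), 0.2 ± 0.1 (grip) and 3.5 ± 4 (MFI), so d = 1.07, 2.0 and 0.875. It states 25 to 42 per group and enrols 60 after 30% dropout.
- Dropout: 42/0.70 = 60, reproduced.
- Size per group: n = 2(1.960 + 0.842)²/d² = 15.70/d² gives 14, 4 and 21 (15, 6 and 22 with the t distribution). The range 25 to 42 is not reproduced.
- Hidden alpha split: alpha = 0.05/3 gives 19, 6 and 28, and with 90% power 24, 7 and 36. Neither matches, so the stated range gives no sign that alpha was divided.
- Multiplying the SD by √2 gives 28, 8 and 42, which matches only the upper end. This matters for the cost (step 5).

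**2. Counting candidates in section 9.1.**
- Fitness: 11 exercise-test values.
- Strength: 2 (grip, each side) + 1 (chair stand) + 1 (quadriceps) = 4.
- Fatigue: 5 + 4 = 9.
- Total: 11 + 4 + 9 = 24. It is 23 if grip is one variable, and 28 if the four lung-function values are added.

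On the section 11.1 reading the count is 3, or 1 + 1 + 5 = 7 if every MFI subscale counts.

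**3. Family-wise error, if any one result below 0.05 counts as success.** For k independent tests it is 1 − 0.95^k. For tests with common correlation ρ (assumed; the protocol gives none) it is 1 − ∫[Φ((1.96 − √ρ·x)/√(1−ρ)) − Φ((−1.96 − √ρ·x)/√(1−ρ))]^k φ(x)dx.

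| Reading | k | ρ = 0 | ρ = 0.3 | ρ = 0.5 | ρ = 0.7 |
|---|---|---|---|---|---|
| One measure per domain | 3 | 14.3% | 13.6% | 12.5% | 10.9% |
| All MFI subscales, VO2max, grip | 7 | 30.2% | 27.2% | 23.0% | 17.8% |
| All candidates | 24 | 70.8% | 59.5% | 45.8% | 31.1% |

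**4. What the success rule changes.** Had the protocol required all three domains to be positive, testing each at 0.05 would need no adjustment. It states neither rule, so the table is conditional on the any-one rule.

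**5. Power under Holm.** The first step uses 0.05/3 = 0.0167. With n = 42 evaluable per arm, power ≈ Φ(d√(n/2) − z), where √21 = 4.583 and z = 2.394.
- MFI, stated inputs: 0.875 × 4.583 − 2.394 = 1.616, so 94.7% (93.9% with the t distribution).
- VO2max: 1.071 × 4.583 − 2.394 = 2.516, so 99.4% (99.2%).
- Grip: above 99.9%.
- If 42 per arm really gives 80% at 0.05, then d = 0.62: 0.62 × 4.583 − 2.394 = 0.45, about 67% (65% with the t distribution).
- The difference detectable with 80% power rises from 0.62 to 0.72 SD.

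**The case against.** **What stands.**
- Section 11.1 does point to VO2max, hand grip and MFI as the primary outcomes. The most natural reading is three measures, so it would be wrong to say the protocol has no primary variable.
- The exercise-test list describes what the test yields and does not declare each value an endpoint. Maximal heart rate and oxygen saturation look more like test outputs than efficacy outcomes.
- Alpha of 0.05 appears only in the sample-size paragraph. Its use for each test is an inference, though no other level is given.
- A statistical analysis plan, not available here, could hold the adjustment method. Its absence from the protocol is not the point.

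**What a reader might infer, and why it is not supported.** One might conclude that 24 primary tests are each run at 0.05, with a 71% chance of a false claim, and more once two time points are counted. The 71% needs all 24 to be endpoints and independent, whereas many come from one exercise test or one questionnaire. Both follow-ups enter a single model and separate tests at t=1 and t=2 are not stated, so doubling the count has no basis in the text. Nor does section 11.1 name MFI general fatigue or t=1, so neither may be presented as already chosen.

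**What does not stand.** The three-measure reading does not settle the matter. The MFI score, the grip summary, the contrast and the success rule remain open. Sections 6, 9.1, 9.2 and 11.1 conflict with one another, and a separate analysis plan would not remove that conflict from the protocol.

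**Conclusion.** The primary definition is contradictory and badly fixed within the protocol itself. If any one primary result counts as success at two-sided 0.05, family-wise error is about 14% for three independent tests (11-14% at assumed correlations of 0.7 to 0.3) and about 30% for seven independent tests. The worst case of 24 measures gives 31-71%, as the assumed correlation falls from 0.7 to 0, and it is an upper bound on the ambiguity, not a description of what is planned. These figures rest on the any-one rule, on 0.05 per test and on assumed correlations; an all-three rule would avoid the inflation, but the protocol does not state one. The placing of quality of life and the position of the FQL are labelling conflicts that stand whatever the error rate.

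**What to change.** Align sections 4, 6, 9.1, 11.1 and 11.2.2 before any results by arm are seen:
1. Name one primary variable per domain: VO2max, one pre-named hand-grip summary, and one pre-named MFI score (general fatigue would be a candidate).
2. Pre-specify one treatment contrast from the longitudinal model, for example the difference at T1. The MFI score and the contrast are for the sponsor to choose and record.
3. Test the three by Holm at an overall two-sided 0.05, and state which results support a claim of effectiveness.
4. Make the remaining exercise-test, lung-function and strength measures, the other MFI subscales and the FQL secondary.
5. Move health-related quality of life out of the primary objective, and point section 11.2.3 to the three named measures.

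**Cost.** The wording changes are small; the real cost is power. At 42 evaluable per arm the first Holm step gives 94% for MFI and 99% for VO2max with the stated inputs. If 42 is truly the number that gives 80% at 0.05, MFI power at that step is about 65%. Restoring 80% there would take about 57 evaluable per arm, or 57/0.70 = 81.4, hence 82 enrolled. This is Holm's worst case: the threshold relaxes to 0.025 and then 0.05 as other outcomes are rejected. Because section 11.1 does not reproduce its own 25 to 42, the sponsor should state which inputs apply and report the resulting power alongside the change.
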